### Visit Windows for █████ PsAID-12, BASDAI, █████, PASI, LDI, Enthesitis evaluation (LEI+SPARCC enthesitis index)

| Nominal Week | Nominal Study Day | Visit Window                                          |
|--------------|-------------------|-------------------------------------------------------|
| 0            | 1                 | All assessments prior to the start of study treatment |
| 4            | 29                | Day 2 – 43                                            |
| 8            | 57                | Day 44 – 71                                           |
| 12           | 85                | Day 72 – 99                                           |
| 16           | 113               | Day 100 – 127                                         |
| 20           | 141               | Day 128 - 155                                         |
| 24           | 169               | Day 156+                                              |

### Visit Windows for Safety Laboratory Testing (hematology and chemistry) and ESR

| Nominal Week | Nominal Study Day | Visit Window                                          |
|--------------|-------------------|-------------------------------------------------------|
| 0            | 1                 | All assessments prior to the start of study treatment |
| 4            | 29                | Day 2 – 43                                            |
| 8            | 57                | Day 44 – 71                                           |
| 12           | 85                | Day 72 - 99                                           |
| 16           | 113               | Day 100 - 127                                         |
| 20           | 141               | Day 128 - 155                                         |

## Visit Windows for Safety Laboratory Testing (hematology and chemistry) and ESR

| Nominal Week      | Nominal Study Day | Visit Window  |
|-------------------|-------------------|---------------|
| 24                | 169               | Day 156 - 190 |
| Safety Follow-up* | 211               | Day 191+      |

\*Subjects who discontinued early, a safety follow-up period of 8 weeks after the last dose of study treatment

## Visit Windows for Safety Laboratory Testing ( Urinalysis)

| Nominal Week      | Nominal Study Day | Visit Window                                          |
|-------------------|-------------------|-------------------------------------------------------|
| 0                 | 1                 | All assessments prior to the start of study treatment |
| 4                 | 29                | Day 2 – 57                                            |
| 12                | 85                | Day 58 - 99                                           |
| 16                | 113               | Day 100 - 141                                         |
| 24                | 169               | Day 142 - 190                                         |
| Safety Follow-up* | 211               | Day 191+                                              |

\*Subjects who discontinued early, a safety follow-up period of 8 weeks after the last dose of study treatment

## Visit Windows for PtGADA, PtAAP, HAQ-DI, hs-CRP, PhGADA, TJC68 and SJC66

| Nominal Week | Nominal Study Day | Visit Window                                          |
|--------------|-------------------|-------------------------------------------------------|
| 0            | 1                 | All assessments prior to the start of study treatment |
| 2            | 15                | Day 2 – 22                                            |
| 4            | 29                | Day 23 – 43                                           |
| 8            | 57                | Day 44 – 71                                           |
| 12           | 85                | Day 72 – 92                                           |
| 14           | 99                | Day 93 - 106                                          |
| 16           | 113               | Day 107 - 127                                         |
| 20           | 141               | Day 128 - 155                                         |
| 24           | 169               | Day 156+                                              |

## Visit Windows for ADA and PK Sampling

| Nominal Week      | Nominal Study Day | Visit Window                                          |
|-------------------|-------------------|-------------------------------------------------------|
| 0                 | 1                 | All assessments prior to the start of study treatment |
| 2                 | 15                | Day 2 – 22                                            |
| 4                 | 29                | Day 23 – 43                                           |
| 8                 | 57                | Day 44 – 71                                           |
| 12                | 85                | Day 72 – 92                                           |
| 14                | 99                | Day 93 - 106                                          |
| 16                | 113               | Day 107 - 127                                         |
| 20                | 141               | Day 128 - 155                                         |
| 24                | 169               | Day 156 - 190                                         |
| Safety Follow-up* | 211               | Day 191+                                              |

\*Subjects who discontinued early, a safety follow-up period of 8 weeks after the last dose of study treatment

## Visit Windows for SF-36v2, FACIT-Fatigue

| Nominal Week | Nominal Study Day | Visit Window                                          |
|--------------|-------------------|-------------------------------------------------------|
| 0            | 1                 | All assessments prior to the start of study treatment |
| 4            | 29                | Day 2 – 57                                            |
| 12           | 85                | Day 58 - 99                                           |
| 16           | 113               | Day 100 - 127                                         |
| 20           | 141               | Day 128+                                              |

## Visit Windows for ECG

| Nominal Week      | Nominal Study Day | Visit Window                                          |
|-------------------|-------------------|-------------------------------------------------------|
| 0                 | 1                 | All assessments prior to the start of study treatment |
| 12                | 85                | Day 2 – 148                                           |
| Safety Follow-up* | 211               | 149+                                                  |

\*Subjects who discontinued early, a safety follow-up period of 8 weeks after the last dose of study treatment

## Visit Windows for BSA and mNAPSI

| Nominal Week | Nominal Study Day | Visit Window                                          |
|--------------|-------------------|-------------------------------------------------------|
| 0            | 1                 | All assessments prior to the start of study treatment |
| 12           | 85                | Day 2 – 127                                           |
| 24           | 169               | 128+                                                  |

## Visit Windows for Vital Signs

| Nominal Week      | Nominal Study Day | Visit Window                                          |
|-------------------|-------------------|-------------------------------------------------------|
| 0                 | 1                 | All assessments prior to the start of study treatment |
| 2                 | 15                | Day 2 – 22                                            |
| 4                 | 29                | Day 23 – 36                                           |
| 6                 | 43                | Day 37 – 50                                           |
| 8                 | 57                | Day 51 – 64                                           |
| 10                | 71                | Day 65 – 78                                           |
| 12                | 85                | Day 79 – 92                                           |
| 14                | 99                | Day 93 - 106                                          |
| 16                | 113               | Day 107 - 120                                         |
| 18                | 127               | Day 121 - 134                                         |
| 20                | 141               | Day 135 - 148                                         |
| 22                | 155               | Day 149 - 162                                         |
| 24                | 169               | Day 163 - 190                                         |
| Safety Follow-up* | 211               | Day 191+                                              |

\*Subjects who discontinued early, a safety follow-up period of 8 weeks after the last dose of study treatment

## 7.3 Handling of Missing Data and Randomization Stratification Errors

### 7.3.1 Missing Data Analysis Methods

Missing data in this study may result from participants discontinuing from the study prematurely or missing intermediate visits or selected assessments while remaining on study. Every reasonable effort will be made to obtain the protocol-required data for all study assessments that are scheduled for all participants who have been enrolled.

## Dichotomous Efficacy Endpoints

For all dichotomous endpoints, a non-responder imputation method will be used for the primary analysis. Participants will be considered non-responders if:

- They discontinue the study prior to the Week 12 visit for Part A or prior to the Week 24 visit for Part B and Part A+B (due to any reason). All future visits following the discontinuation will be imputed, or
- Have missing data for the endpoint of interest at baseline or at any intermediate time points. All visits with a missing assessment will be imputed, or
- Take prohibited protocol medication prior to the Week 12 visit for Part A or Week 24 visit for Part B and Part A+B. All future visits following the start date of the prohibited medication will be imputed.

In addition, two sensitivity approaches will be used for the dichotomous primary and key-secondary endpoints for analyses data:

1. The method for handling missing data will be dependent on the reason the data are missing. If a participant has discontinued due to lack of efficacy or an adverse event or starting prohibited medication the data will be imputed as a non-response. If the data are missing for any other reason the data will not be imputed. A multiple imputation for primary and key secondary analysis will be used including all available data up to Week 12 to enable the inclusion of participants with missing data at Week 12.
2. No data will be imputed and the data analysed by visit based on the observed data only.

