### **7.2 Endpoints**

#### **7.2.1 Primary Endpoint and Estimand**

##### **7.2.1.1 Primary Estimand**

The primary estimand assesses treatment success at Week 12 defined as achieving an ACR50 response. A treatment failure at Week 12 will be defined as not achieving an ACR50 response, discontinuing treatment for any reason prior to Week 12, or receiving prohibited medication. The attributes of the primary estimand are as follows:

- Target population: adults with a confirmed diagnosis of PsA per the 2006 CASPAR [[Taylor W. et al., 2006](#)] with symptoms for  $\geq 6$  months prior to the Screening Visit;
- Treatment: sonelokimab at 3 different regimens: sonelokimab 120 mg Q2W, sonelokimab 60 mg Q2W, or sonelokimab 60 mg Q4W;
- Primary endpoint: is percentage of participants achieving ACR50, i.e., at least 50% improvement in the ACR response criteria at Week 12 compared with baseline;

- Intercurrent events: intercurrent events include the following:
  - Use of prohibited concomitant medication (Section 10.5): participants will be analyzed as a treatment failure after taking prohibited medication, i.e., non-responder imputation will be performed after the first episode of prohibited medication for all future assessments (composite strategy);
  - Withdrawal from treatment due to any reason (Section 9.6): participants will be considered non-responders to treatment if they discontinue the study prior to the Week 12 Visit (composite strategy);
  - Study treatment non-adherence (missing doses) or drug administration error: participants will be analyzed the same if the event occurs or not (treatment policy strategy).
- Population level summary: the primary estimator will be the improvement compared to placebo during the 12-week Part A based on the primary endpoint.

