### **9.4 Study Treatment Discontinuation**

The investigator should discontinue study treatment of a given participant if, on balance, they believe that continuation would be detrimental to the participant's well-being or if the participant plans to initiate any therapies outlined in the prohibited medications list in Section 10.5.1. EOT procedures should be performed at the point when the decision to discontinue the treatment has been made. A Safety Follow-up Visit should be performed 8 weeks ( $\pm 7$  days) after their last dose of study treatment.

In addition to the EOT Visit, participants who decide to discontinue the treatment in Part A should continue to attend all future scheduled visits through Week 12 for safety and efficacy assessments. A separate Safety Follow-up Visit is not required if the participant attends a scheduled visit at 8 weeks after treatment discontinuation.

If the patient discontinues treatment in Part B, EOT procedures should be performed at the point when the decision to discontinue the treatment has been made. A Safety Follow-up Visit should be performed 8 weeks ( $\pm 7$  days) after their last dose of study treatment.

In case the participant does not agree to continue with all scheduled visits, the participant will be withdrawn from the study.

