#### **12.3.2.1 Primary Analysis**

For the primary analysis, the hypotheses to be tested are that the proportion of participants who achieve ACR50 at Week 12 compared with baseline in the sonelokimab 120 mg Q2W, sonelokimab 60 mg Q2W, or sonelokimab 60 mg Q4W arms are different from that of the placebo arm.

Only the sonelokimab 120 mg Q2W, sonelokimab 60 mg Q2W, and sonelokimab 60 mg Q4W arms will be compared pairwise with placebo. A comparison among dose arms (sonelokimab 120 mg Q2W, sonelokimab 60 mg Q2W, and sonelokimab 60 mg Q4W) is not planned. [REDACTED]

A logistic regression model will be used to test the pairwise comparisons (placebo and either sonelokimab 120 mg Q2W, sonelokimab 60 mg Q2W, or sonelokimab 60 mg Q4W) including fixed effects for treatment and the stratification factors (sex and exposure to biologic agents prior to the Screening Visit). Results will be presented in terms of odds ratios, as well as risk difference, 95% CI, and estimated p-value.

For the primary analysis, a non-responder imputation method will be used. Participants will be considered non-responders to treatment if they discontinue the study prior to the Week 12 Visit due to any reason, have a missing ACR50 score at baseline or at the Week 12 Visit due to any reason, or take prohibited medication prior to the Week 12 Visit.

The sensitivity estimand for the primary endpoint will be analysis using a Generalized Linear Mixed Model (GLMM) to account for any missing data due to withdrawals for reasons other than lack of efficacy or taking prohibited medications. The model will include fixed effects for treatment, sex, prior biologic use, visit, treatment by visit interaction. The correlations between repeated measures will be modeled using an unstructured covariance matrix.

The primary analysis will be performed using the FAS.

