| Population-level summary                           | The primary estimator will be the improvement compared to placebo over the 12-week based on ACR50.                                                                                                                                                                                                                                                                                                                                                                                                                                                                                                                                                                                                                                                                                                  |
| Intercurrent events and strategies to handle those | 
 
• Use of prohibited concomitant medication (Section 10.5.1 of protocol): participants will be analyzed as a treatment failure after taking prohibited medication, i.e., non-responder imputation will be performed after the first episode of prohibited medication for all future assessments (composite strategy);
 
• Withdrawal from treatment due to any reason (Section 9.6 of protocol): participants will be considered non-responders to treatment if they discontinue the study prior to the Week 12 (composite strategy);
 
• Study treatment non-adherence (missing doses) or drug administration error: participants will be analyzed in the same way as if the event had occurred or not (treatment policy strategy).
 
 |

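### Primary endpoint: the estimand counts stopping treatment before Week 12 as failure, but the non-responder rules are triggered only by leaving the study

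*Combined protocol and SAP*

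**What the plan says.** The failure definition in protocol 7.2.1.1 lists, besides not reaching ACR50, "discontinuing treatment for any reason prior to Week 12, or receiving prohibited medication". The handling is labelled composite.

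The rules that turn this into data use another event:

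- Protocol 12.3.2.1: "Participants will be considered non-responders to treatment if they discontinue the study prior to the Week 12 Visit due to any reason".
- SAP 7.3.1, for dichotomous endpoints: "They discontinue the study prior to the Week 12 visit for Part A".
- SAP 5.1: "Withdrawal from treatment due to any reason (Section 9.6 of protocol): participants will be considered non-responders to treatment if they discontinue the study". This bullet names one event in its heading and another in its rule. The matching bullets in protocol 7.2.1.1 and, for the key secondary endpoints, in protocol 7.2.2.1 and SAP 5.3 are mixed in the same way.

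Stopping treatment and leaving the study are separate events here. Protocol 9.4 says that "participants who decide to discontinue the treatment in Part A should continue to attend all future scheduled visits through Week 12", for safety and efficacy. Only those who will not continue the visits are withdrawn from the study.

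**The concern.** The primary analysis is meant to estimate the composite estimand. If non-response is imputed only for people who leave the study, those who stop treatment but stay contribute their observed Week 12 result. For that event the handling is treatment policy, not composite. ACR50, ACR20 and PASI90 are all affected.

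At stake is who counts as a responder on the primary endpoint. With conflicting texts, the programmer has to choose between two rules, and the SAP's own wording points to the one that departs from the failure definition. Because both Q2W doses must pass before the key secondary endpoints and then the 60 mg Q4W arm are tested, one ACR50 classification can affect the rest of the sequence.

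**Working it through.** **1. Can a participant fall in the gap?** Take someone who stops treatment before Week 12, stays in the study, takes nothing prohibited and has a complete Week 12 assessment that meets ACR50.

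| Text | Trigger | Classification |
|---|---|---|
| Protocol 7.2.1.1, failure definition | stopping treatment | failure |
| Protocol 7.2.1.1 and SAP 5.1, event bullet | headed treatment, triggered by study | unclear; responder if the trigger is read literally |
| Protocol 12.3.2.1 | leaving the study, missing data, prohibited medication | responder |
| SAP 7.3.1 | leaving the study, missing data, prohibited medication | responder |

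SAP 8.6.2.1 does not close the gap. It applies non-responder imputation to missing data and points to SAP 7.3.2, which deals with incomplete dates. SAP section 9 lists no change from the protocol that would explain the different trigger.

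The case is plausible. Protocol 9.4.1 requires treatment to stop for reasons unrelated to response, such as laboratory findings. In Part A the last active sonelokimab dose is at Week 8, so someone in a sonelokimab arm who stops after that visit has had every active dose.

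**2. The plan's own figure.** Inputs from protocol 12.1 and SAP 5.5: 40 per arm, 40% vs 10%, two-sided alpha 0.025. Pooled-variance normal approximation, mean rate 0.25:

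- z for 1 − 0.0125 = 2.2414
- √(2 × 0.25 × 0.75) = 0.6124
- √(0.4 × 0.6 + 0.1 × 0.9) = 0.5745
- (0.30 × √40 − 2.2414 × 0.6124) / 0.5745 = 0.9135
- power = Φ(0.9135) = 81.95%

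This agrees with the stated power of more than 80%.

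**3. Weight of one participant.** 1/40 = 2.5 points, against a planned difference of 30 points. Unadjusted pooled chi-square, z = (p1 − p2) / √(2p̄(1 − p̄)/40):

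| Active vs placebo responders, of 40 each | z | two-sided p |
|---|---|---|
| 16 vs 4 (design rates) | 3.098 | 0.0019 |
| 15 vs 4 | 2.890 | 0.0039 |
| 14 vs 4 | 2.677 | 0.0074 |
| 13 vs 4 | 2.460 | 0.0139 |
| 12 vs 4 | 2.236 | 0.0253 |
| 12 vs 3 | 2.578 | 0.0099 |

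From 13 vs 4, losing one active responder crosses 0.025. From 12 vs 4, losing one placebo responder moves the result the other way, to 0.0099. An unadjusted logistic Wald test behaves similarly (12 vs 4, p = 0.032; 13 vs 4, p = 0.019). The planned model also adjusts for sex and prior biologic use, so its p-values will differ.

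**4. Planning power, by assumption.** The documents give no rate of treatment discontinuation. Suppose 40% and 10% are the rates under the rule as written, and a share d of each arm stops drug, stays and responds at the arm's rate. Counting these people as failures multiplies both rates by (1 − d):

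- d = 5%: 38.0% vs 9.5%, power 78.8%
- d = 10%: 36.0% vs 9.0%, power 75.4%

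If they respond at half the arm's rate, power is 80.4% and 78.8%. If the planning rates already count these people as failures, planned power does not change.

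**The case against.** The strongest reply is that the text is mixed, not plainly wrong. The event bullets are headed as withdrawal from treatment and labelled composite, and a careful programmer could apply the failure definition. The bullets also cite protocol 9.6, on withdrawal of participants, and only protocol 7.2.1.1 states the failure definition outright. One could therefore keep the study trigger and make the estimand treatment policy for this event. The affected group is narrow, and the second sensitivity estimand already reports a treatment-policy result.

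Much of this stands. It limits the size of the problem and shows that a reader could resolve the conflict either way. It does not remove the conflict: SAP 7.3.1 and protocol 12.3.2.1 give the study trigger without qualification. The description of the first sensitivity estimand also shows the likely intent. It adds off-treatment data through Week 12 to the primary estimand, which makes sense only if the primary estimand leaves those data out.

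Two stronger readings are tempting and not supported:

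- *The first sensitivity analysis is stricter than the primary one.* SAP 8.6.2.1 sets people who discontinued for efficacy or an adverse event to non-response, but does not say from what they discontinued. SAP 5.2 uses the study trigger. The ordering reverses only if stopping treatment is meant.
- *The rule favours sonelokimab or decides the trial.* No document gives a count by arm. Reclassified placebo responders would widen the difference, and at the design rates the loss of three active responders leaves p = 0.0139.

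**Conclusion.** The point holds as a conflict between the stated primary estimand and the rules that implement it. Followed as written, the SAP counts some participants as responders whom protocol 7.2.1.1 defines as failures, and the key secondary rules carry the same ambiguity. It should be settled before unblinding because it determines responder status on the primary endpoint.

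The size is unknown. It depends on how many people stop drug, stay to Week 12, take nothing prohibited and respond, and in which arms. That number may be zero. The figures of 2.5 points per participant, the p-values near 0.025 and the power scenarios are illustrations, not estimates of bias. They rest on 40 per arm and, for the p-values, on an unadjusted test. The 0.025 limit applies only to the smaller of the two Q2W p-values.

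**What to change.** Before unblinding:

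1. In SAP 5.1, 5.3 and 7.3.1, and in protocol 7.2.1.1, 7.2.2.1 and 12.3.2.1, make the trigger *discontinue study treatment or the study before the Week 12 visit, for any reason*.
2. State that the trigger is the recorded premature discontinuation of study treatment (protocol 9.5), so that it is not confused with a missed dose, which both documents handle by treatment policy.
3. In the first sensitivity estimand (protocol 7.2.1.2 and 7.2.2.2, SAP 5.2 and 5.4) and in SAP 8.6.2.1, say that discontinuation for lack of efficacy, or in the SAP also for an adverse event, means discontinuation of treatment.
4. Cite protocol 9.4 alongside 9.6 in these bullets, and correct the SAP 8.6.2.1 reference from 7.3.2 to 7.3.1.
5. Keep the observed off-treatment Week 12 data for the sensitivity estimands.

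If treatment policy is what the sponsor wants for this event, the failure definition and the composite label would have to change instead, and the first sensitivity estimand would need a new description.

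The cost is wording in the SAP and a matching protocol clarification. Visits and data collection do not change. Reported response rates may be slightly lower.
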